## Abstract

**Background:**

Nonmuscle invasive bladder cancer (NMIBC) is a chronic condition requiring intensive follow-up, repeated endoscopic examinations, tumor resections, and intravesical treatments that can occur every 3 months for life. In this clinical context, patient-reported outcomes (PROs) are a critical concern for patients and their managing clinicians. PROs have enormous potential to be integral to treatment assessment and recommendations for NMIBC; however, current PRO measures are inadequate for NMIBC because they lack key NMIBC-specific symptoms and side effects associated with contemporary treatments.

**Objective:**

The overarching aim of this study was to develop and evaluate a patient-reported symptom index (SI) for individuals with NMIBC (the NMIBC-SI) that is acceptable to patients; reliable, valid, and responsive to differences between contemporary treatments for NMIBC; and fit for purpose as an endpoint in clinical trials.

**Methods:**

The NMIBC-SI will be evaluated in 2 field tests across a total of 3 years. Field test 1 is a cross-sectional study design involving 225 adult NMIBC patients recruited while undergoing active treatment or those who completed final treatment within the past week. Data collected include patient demographics, clinical features of the tumor, risk category, treatment type, comorbidity, and PROs. Field test 2 is a prospective longitudinal study involving 225 newly diagnosed NMIBC-SI patients. Clinical data and patient-completed questionnaires will be collected at 4 time points during treatment: before tumor resection, 1 week after resection, end-of-induction intravesical therapy, and 1-year follow-up. Standard psychometric tests will be performed to assess the reliability, validity, responsiveness, and clinical utility of the NMIBC-SI.

**Results:**

Participant recruitment to field test 1 commenced in February 2017. Recruitment for field test 2 is planned to commence in January 2018. Final results are expected to be published in 2019. The NMIBC-SI will be freely available for use via registration.

**Conclusions:**

This study protocol contains detailed methods that will be used across multiple international sites. Phase 2 in the development of the NMIBC-SI will enable a comprehensive evaluation of its reliability, validity, and responsiveness to ensure that the NMIBC-SI is fit for purpose in clinical research and provides an evidence base for the ongoing improvement of future therapies for NMIBC.

**Trial Registration:**

ClinicalTrials.gov NCT03091764; http://clinicaltrials.gov/ct2/showNCT03091764 (Archived by WebCite at http://www.webcitation.org/6umBhQeNX)

## Introduction

### Nonmuscle Invasive Bladder Cancer Is a Chronic Health Problem

Bladder cancer is the 9th most common cancer diagnosed worldwide and the 13th most common cause of cancer death [1]. Internationally, 430,000 new cases of bladder cancer were diagnosed in 2012, with 165,000 recorded deaths [2]. In Australia alone, in 2014, an estimated 2730 people were diagnosed with bladder cancer [3], and there were 1040 recorded deaths from it [1,4]. Bladder cancer is 3 to 4 times more prevalent in males than in females, and incidence increases with age, with people older than 55 years accounting for 90% of new diagnoses [5]. Around 75% of bladder cancer diagnoses are not muscle invasive at first diagnosis [6]. Because 5-year survival in this group exceeds 80% [7], the prevalence of nonmuscle invasive bladder cancer (NMIBC) is 10 times its incidence, even though the overall rate of recurrence is approximately 60% to 70% and progression is 20% to 30% [8].

Nonmuscle invasive bladder cancer is a chronic disease. Its management depends on the risk of the bladder cancer recurring and progressing [6]: low-risk patients receive frequent cystoscopies, possible tumor resections, and single instillations of postoperative chemotherapy; intermediate-risk patients usually require intravesical therapy, which lasts between 6 weeks and 3 years; and high-risk patients require intravesical Bacillus Calmette–Guérin (BCG; immunotherapy), which starts with 6-week induction treatment and continues with maintenance for 1 to 3 years. The higher the risk, the more the requirement for intravesical therapy. Follow-up is mandatory, with repeated endoscopic examinations, radiological imaging, biopsies, and tumor resections as frequent as 3-monthly and life-long. This makes the cost per patient from diagnosis to death the highest of all cancers [9], contributing a major economic and resource burden on health care systems [9].

Guidelines for the management of NMIBC are based on evidence for the effectiveness of treatments in reducing risk of bladder cancer progression and recurrence. Evidence for reductions in health-related quality of life (HRQoL) and associated side effects with each treatment are not incorporated into the decision-making process because they have been poorly documented (see section below on Critical Gaps in Knowledge About HRQoL and Patient-Reported Outcomes [PROs] in NMIBC). This is despite the fact that these treatments can cause substantial side effects and local and systemic toxicity. For example, the commonly used BCG has proved effective in reducing recurrences in patients with high-grade tumors and carcinoma in situ, but it can cause moderate to severe local and systemic side effects, and only 16% are able to complete their full treatment schedule [10].

### Why Patient-Reported Outcomes Are Important

A PRO is any report that comes directly from patients about how they feel in relation to their health condition and its therapy, without interpretation by others [11]. PROs can include symptoms, function, HRQoL, and perceptions of treatment. These patient reports are captured and quantified by patient-reported outcome measures (PROMs) in the form of questionnaires.

PROs are beneficial for improving patient-clinician communication, prioritizing patient-centered care, and improving service provision [12,13]. In contrast to life-threatening conditions where survival endpoints may dominate HRQoL considerations, PROs should be key considerations in chronic conditions [14]. For example, a treatment found to be effective in improving survival in a clinical trial may fail in the real world because of toxicity and reduced HRQoL, which could compromise compliance and subsequently its effectiveness [15]. Similarly, the inconvenience of repeated clinic visits for monitoring or treatment can compromise compliance [16]. The acceptance of PROM-based evidence by regulatory bodies is reflected in the US Food and Drug Administration’s (FDA) approval of PROs to support product labeling claims [17].

### Critical Gaps in Knowledge About HRQoL and PROs in NMIBC

The primary goal in managing NMIBC in patients is to completely remove the tumor and control the unpredictable risk of recurrence and progression to muscle invasion [18] with as little treatment burden and side effects as possible. We know from clinical experience that there are many possible adverse consequences and substantial reductions in HRQoL that differ between treatment options such as chemotherapy versus BCG, induction versus maintenance therapy, and impact of single instillation chemotherapy. However, these have not been well studied or reported, and the key data on PROs are lacking for NMIBC.

The most recent indexed comprehensive review of the literature investigating the impact of NMIBC on HRQoL is over 14 years old and is based on research published between 1966 and 2000 [19]. Our recent systematic review of PROMs in NMIBC (manuscript under review; [name] et al) found only 6 out of 19 papers that assessed PROs used a standardized measure. Other limitations of these studies include lack of comparison groups, poor adjustment for baseline physical and psychological functions, failure to distinguish between patients with varying degrees of risk and between treatments in the analysis, and small sample sizes. Consequently, key evidence on the impact of tumor resections, repeated cystoscopies, single chemotherapy instillations, multiple chemotherapy instillations, and BCG therapies on patients’ HRQoL is lacking.

Our review did identify a NMIBC-specific PROM, the European Organisation for Research and Treatment of Cancer (EORTC)—EORTC QLQ-BLS24 questionnaire—developed in 1996. There is no publicly available information detailing its development, and it only recently underwent validation, 18 years after its development (now renamed the EORTC QLQ-NMIBC24) [20]. The validation study had some limitations: it was based on data from a single clinical trial, including only high- and intermediate-risk patients with little information about their treatments; the original content was not reviewed against contemporary treatments (which differ considerably from those in use before 1996 when the original content was developed); modifications to the scale structure were informed by clinical evidence only (ie, no patient perspective); and there is lack of assessment of test-retest reliability and clinical validity (eg, whether the module distinguishes between different risk groups for NMIBC) [20]. The question remains whether the EORTC QLQ-NMIBC24 adequately captures the impact of important symptoms and side effects associated with contemporary treatment for NMIBC.

Therefore, a patient-reported NMIBC-specific symptom index (NMIBC-SI), including possible symptoms and side effects of contemporary treatments for NMIBC, is needed to enable accurate, robust, and clinically relevant assessment of differences in PROs among contemporary treatments and to provide an evidence base for the ongoing improvement of future therapies for NMIBC. Such a measure has been developed based on existing literature and interviews with patients and clinicians [21] and pretested for face validity, comprehensiveness, comprehensibility, and clinical utility through interviews with key stakeholders (patients, urologists, and specialist nurses).

### Aims and Objectives

The overarching aim of this study was to develop and evaluate the NMIBC-SI for reliability, validity, and responsiveness to ensure that it is fit for purpose in clinical research.

#### Psychometric Aims

To evaluate the feasibility and acceptability of the NMIBC-SI; produce a shorter version, if appropriate, by selecting items that perform best against robust psychometric criteria; examine the legitimacy of summing items into scales; identify legitimate scales and subscales; and test scaling assumptions and scale performance in a large-scale Australian sample (field test 1).To psychometrically evaluate the measurement properties of the final version SI, testing for reliability, clinical validity (sensitivity to differences between patient groups and responsiveness to clinically important change), and interpretability of the final version NMIBC-SI in a new large-scale international sample (field test 2).To conduct a head-to-head comparison of the new NMIBC-SI with the EORTC bladder cancer module, QLQ-NMIBC24.

#### Clinical Aims (Field Test 2)

To assess and compare key PROs across the full range of contemporary treatments for NMIBC and over-the-disease trajectory, including acute treatment and 1-year survivorship.To compare PROs between patients with low-, intermediate-, and high-risk NMIBC.

## Methods

### Overview of Project Research Design

This multicenter study was designed to evaluate the psychometric properties of an NMIBC-SI for patients treated for NMIBC. Guidance for developing and validating health outcome measures has been followed to ensure high quality and standardization for the development of the NMIBC-SI [11,22,23]. The guidance recommends that collaboration and expert discussion are sought and utilized through all stages of development, and it proposes distinct phases for the development and evaluation of PROMs. The research design includes 2 phases: (1) development of NMIBC-SI in 2 parts, conceptual framework to generate items and pretesting; and (2) evaluation of NMIBC-SI in 2 parts, a preliminary field test 1 for item reduction and a final field test 2 for psychometric properties (Figure 1). Phase 1 has been conducted, and results are summarized below.

In preliminary research and phase 1 development, a conceptual framework was developed by tapping into 3 sources: (1) a systemic review and narrative analysis of the HRQoL and PRO literature, identifying several local and systematic side effects associated with contemporary treatments for NMIBC (eg, urinary problems, discomfort, and malaise); (2) in-depth qualitative interviews with a sample of NMIBC patients that explored patients’ experience of receiving treatment; and (3) in-depth qualitative interviews with treating clinicians (specialist nurses and urologists) that explored important issues from their perspective. This phase was important to ensure that high content validity was achieved and demonstrated [24]. An exhaustive list of clinically relevant issues (items) was generated from the conceptual framework and patient verbatims [21].

In phase 1 pretesting, further qualitative interviews explored the generated list of issues with patients and clinicians for clarity and overlap and the appropriateness of the NMIBC-SI’s time frame, question stem, and response options. On the basis of information obtained from the interviews, the provisional NMIBC-SI was revised to produce a preliminary version ready for field testing.

The evaluation of the NMIBC-SI is phase 2 of this project. It will be undertaken in 2 parts: preliminary field test 1 (item reduction) and final field test 2 (psychometric properties). The preliminary field test will identify any items with poor psychometric performance for possible elimination. The final field test will be undertaken to evaluate the item-reduced version of the NMIBC-SI for reliability, validity, and responsiveness. Gold standard psychometric methods will be used [11,22,23].

### Phase 2: Field Test 1

The psychometric properties of the NMIBC-SI will be evaluated in 2 field tests, including a preliminary field test (item reduction) to identify items with poor psychometric properties for possible elimination and to identify subscales, and a final field test (psychometric evaluation) to evaluate the reliability and validity of the item-reduced version of the NMIBC-SI. The overall strategy and methods for the psychometric evaluation are based on the methods used to develop and validate PROMs in several other areas of medicine and surgery [24-26].

#### Design for Preliminary Field Test 1 (Item Reduction)

The purpose of the preliminary field test 1 is to produce a short (item-reduced) version of the NMIBC-SI and to undertake an initial psychometric evaluation of the item-reduced questionnaire. This will be done using a cross-sectional study design.

An item reduction strategy developed for evaluation of PROMs in other medical areas [25-27] will be used to: (1) identify items on the provisional version of the NMIBC-SI with poor psychometric properties for possible elimination; (2) conduct a preliminary evaluation of NMIBC-SI subscales; and (3) undertake a preliminary evaluation of the acceptability, reliability, and validity of the item-reduced NMIBC-SI.

**Figure 1 figure1:**
[figure not shown]
Development and evaluation of the symptom index for individuals with nonmuscle invasive bladder cancer.

Results of the item reduction analyses will be used to develop a shorter version of NMIBC-SI for final psychometric field testing.

#### Eligibility

##### Inclusion Criteria

Adult patients (aged ≥18 years) from participating centers diagnosed with NMIBC, who are able to read and understand English and give their written informed consent will be included in the study. Patients will be recruited while undergoing active treatment (ie, 1 week after tumor resection or intravesical therapy) or when they have completed final treatment for NMIBC within the past week.

##### Exclusion Criteria

Patients will be excluded from the study if any of the following criteria apply:

They are unconscious or confused.They have cognitive impairment.They are unable to speak, read, and/or write in English.They are diagnosed with muscle invasive disease.They are unable to provide informed consent.

#### Sample Size

Approximately 225 NMIBC patients will be required, purposively sampled to ensure representation of patients across the 3 NMIBC risk categories (Textbox 1) [6]. This sample size is based on recommendations for psychometric analyses of new summated scales; 5 to 10 subjects per item are needed to reduce the chance effect of sampling [28,29]. Following this recommendation, a 30-item NMIBC-SI would require a sample between 150 and 300 patients.

#### Recruitment and Consent Procedures

Patients from participating centers who meet the eligibility criteria will be informed about and invited to take part in the study either in person or via an invitation letter. Consecutive patients will be identified and approached to participate by either the named site investigator or the named site nurse. Accrual will be reviewed to ensure that there is balanced representation of patients in all NMIBC categories. A record of those identified as eligible, approached to participate, refusals, consenting patients, and questionnaire returns will be kept for progress monitoring and final reporting purposes (see Data Collection/Assessment section below).

A verbal explanation of the study and a patient information sheet will be provided for patients to consider. These will include detailed information about the rationale, design, and personal implications of the study. Following information provision, patients will have as much time as they need to consider participation. The right of the patient to refuse consent without giving reasons will be respected.

Assenting patients will then be invited to provide informed, written consent on the consent form at the end of the patient information sheet to collect baseline assessment data and to complete the questionnaire. The patient will remain free to withdraw from the study at any time without giving reasons and without prejudicing any further treatment. The original consent form will be filed within the investigator site file or at a designated secure location.

##### Registration

Following informed consent and confirmation of eligibility, participants will be provided with a study ID number and registered to the study.

##### Screening

The participating site staff will complete a log of all patients screened for eligibility. Screening logs will be returned to the University of Sydney.

Using the study ID number as an identifier, information will be collected for all eligible patients, including the age, gender, risk category, and treatment type.

For those who decline to participate in the study, reasons will be recorded.

Nonmuscle invasive bladder cancer (NMIBC) patient risk groups.High-risk tumorsAny of the following:T1 tumorG3 (high grade, which is a mixture of some G2 and G3) tumorCarcinoma in situ (CIS)Multiple and recurrent and large (>3 cm) Ta G1G2 tumors (all conditions must be presented at this point); low grade is a mixture of G1 and G2Intermediate-risk tumorsAll tumors not defined in the adjacent categories (between the category of low- and high risk)Low-risk tumorsPrimary, solitary, Ta, G1 (PUNLMP, low grade is a mixture of G1 and G2), <3 cm, no CIS

#### Data Collection/Assessment

Study data will be recorded by participating site staff on case report forms and by participants on questionnaire booklets either on paper or electronically. The study data are collected and managed using REDCap electronic data capture tools hosted at the University of Sydney [30].

Assessments will be undertaken as follows:

Registration and baseline dataPatient questionnaire booklet

Registration and clinical data will be completed by the clinician or specialist nurse at participating centers. Hard-copy questionnaires will be collected by the clinician or specialist nurse or posted by the patient back to the site. Study ID number coded data will be sent to the University of Sydney for central data management. Individually identifiable data and master lists linking study ID numbers to individual identity will be retained by the participating sites.

#### Registration and Clinical Data

Patients who meet the inclusion criteria and provide informed consent will be registered to this study. Registration and clinical information will be recorded by participating site staff including the following:

Patient study ID numberAgeGenderCountry of birthMarital statusLiving arrangementsEducationRisk category (clinical definitive category from medical records)Tumor gradeTumor stageTreatment type (information about which treatment interventions the patient is currently receiving)Comorbidity (Charlson Comorbidity Index [31] and history of prostate cancer)Name of site staff member completing clinical dataConfirmation of eligibility

#### Questionnaire Booklet

Participants will self-complete the questionnaire booklet containing the NMIBC-SI, which will be provided to them by the clinician or specialist nurse at participating centers in hard copy or by link to the Web-based version. It is anticipated that completion of the questionnaire may take up to 20 min. Completed hardcopy questionnaires will be entered into REDCap by participating site staff directly or returned to the University of Sydney for data entry.

#### Mode of Questionnaire Administration

Participants will be given a hard copy of the questionnaire or provided with a link to the Web-based questionnaire, depending on their preference.

#### Analyses and Statistical Considerations

To determine whether the NMIBC-SI fulfills fundamental prerequisites for rigorous measurement as defined by established psychometric criteria [32] and the US FDA guidance [11], standard psychometric tests for acceptability, data quality, internal reliability, and factor analysis construct validity will be performed. Table 1, adapted from Gorecki, 2013 [33], presents full details of the tests and criteria used in the psychometric evaluation.

The purpose of the item reduction analysis is to produce a psychometrically robust version of the NMIBC-SI. Standard psychometric tests and criteria, as described in Table 1, will be performed to identify and retain items with strong psychometric properties and eliminate items with poor psychometric properties to produce a shorter, item-reduced version of the NMIBC-SI. These analyses will also evaluate the hypothesized subscales of the NMIBC-SI.

Missing data will not be imputed. The frequency of missing data will be determined, and items with a response rate of <80.0% (180/225) will be investigated.

### Phase 2: Field Test 2—Evaluation of Reliability and Clinical Validity

#### Design for Field Test 2

The purpose of the final field test 2 is to assess the reliability and clinical validity (sensitivity to differences between patient groups and responsiveness to clinically important change) and interpretability of the final version NMIBC-SI in a new large-scale international sample. This phase will be conducted using a prospective longitudinal study design. The outcome will be a patient-reported NMIBC-SI that is reliable and clinically valid, with NMIBC-specific content that complements the more generic HRQoL content of the EORTC QLQ-C30.

#### Eligibility

Adult patients (aged ≥18 years) from participating centers diagnosed with NMIBC, after imaging or flexible cystoscopy but before endoscopic resection, who are able to read and understand English and give their written informed consent will be included in the study.

#### Sample Size

Approximately 225 patients newly diagnosed with NMIBC will be required to provide sufficient subjects for statistical assessment of test-retest reliability [34,35] and clinical validity in terms of both sensitivity to differences between patient groups [36] and responsiveness to clinically important change [37]. See section on Sample Size for Field Test 1 for sample size justification.

**Table 1 table1:** Psychometric tests and criteria.

Property				Definition/test	Criteria for acceptability	
1. Item analysis				Identify items for possible elimination due to weak psychometric performance; assessed on the basis of (1) exploratory factor analysis with principal axis factoring and (2) item- and scale-level analyses	Exploratory factor analysis: items with a factor-loading coefficient ≥0.4 will be retained in each subscale. Applied to all items: (1) missing data <5%; (2) maximum endorsement frequencies <80% (ie, the proportion of respondents who endorse each response category), including floor or ceiling effects <80% (ie, response categories with high endorsement rates at the bottom and top ends of the scale, respectively); (3) evidence of item responsiveness as assessed by significant improvement between baseline and test of cure assessments (field test 2 only)	
2. Acceptability				The quality of data; assessed by completeness of data and score distributions	Missing data for summary scores <20%; normal distribution of endorsement frequencies across response categories (ie, absence of skew, endorsement rates between 0.20 and 0.80); and floor or ceiling effects for summary scores <10%	

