		**Analyses against external criteria**				
			Convergent validity	Evidence that the scale is correlated with other measures of the same or similar constructs; assessed on the basis of correlations between the measure and other similar measures	Correlations are expected to vary according to the degree of similarity between the constructs that are being measured by each instrument. Specific hypotheses are formulated and predictions tested on the basis of correlations	
			Discriminant validity	Evidence that the scale is not correlated with measures of different constructs; assessed on the basis of correlations with measures of different constructs	Low correlations between the instrument and measures of different constructs	
			Known groups differences	The ability of a scale to differentiate known groups; assessed by comparing scores for subgroups that are expected to differ on the construct being measured	Significant differences between known groups or difference of expected magnitude	
5. Responsiveness				The ability of a scale to detect clinically significant change following treatment of known efficacy; assessed by examining within-person change scores before and after treatment and calculating an effect size statistic (mean change score divided by standard deviation of pretreatment scores)	Moderate to large effect sizes (small 0.2, moderate 0.5, and large 0.8 or higher)	

**Table 2 table2:** Patient-reported outcome assessment schedule.

Risk group	Assessed within 3 months before tumor resection	Assessed within 4 to 10 days after the tumor resection	Assessed within 1 month after the end of induction intravesical therapy^a^	Assessed within 1 month before the 1-year cystoscopy (or at early cessation due to adverse events^b^)
High	T1	T2	T3	T4
Intermediate	T1	T2	T3	T4
Low	T1	T2	T3^c^	T4
~n	225	225	225	225

^a^A minimum of 25 participants from each risk group will be asked to complete an additional questionnaire pack 3 to 7 days after T3.

^b^Preferably before cystoscopy.

^c^For the low-risk group, T3 will be 8 weeks after resection.

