#### Analyses and Statistical Considerations

Analyses will evaluate the measurement properties of the final version of the NMIBC-SI, using psychometric tests described for field test 1 (Table 1). Additional tests for reliability (test-retest: correlations for summary scores ≥.70), clinical validity (in terms of sensitivity to groups known to differ clinically and responsiveness to clinically meaningful change over time [37]), and estimation of minimal important difference (interpretability) [39] will be undertaken. Evaluation of subscales will be determined by factor analysis and against external criteria (between-group validity: convergent, discriminant, and known group differences validity). To evaluate convergent and discriminant validity, we will compare NMIBC-SI scales with the scales within the EORTC QLQ-C30 and QLQ-NMIBC24 measures. NMIBC-SI scores for patients by risk and treatment groups will be compared to evaluate known group differences. Risk groups are defined as low, intermediate, and high (see Textbox 1) [6]. Treatment groups are defined as follows: (1) cystoscopy alone or TURBT, (2) course of intravesical chemotherapy, and (3) course of intravesical BCG. We hypothesize that low-risk patients will have lower levels of treatment-related problems at follow-up time points compared with high-risk patients, who have more intensive treatments. Factor analysis, together with the results of other item-level analyses described in Table 1, will be used to investigate hypothesized subscales.

Analyses of the clinical aims will include: (1) evaluation of PRO changes over time, from diagnosis to peak treatment and at 1 year; (2) comparison of PROs between the 3 risk groups at each time point; and (3) head-to-head comparison of the relative discriminatory ability of the NMIBC-SI and the EORTC QLQ-NMIBC24. The pretumor resection assessment (T1) will be at diagnosis and is considered our baseline assessment. Patients are not expected to have any treatment-related problems at this point. The subsequent 3 time points (Table 2) are intended to capture short-term, intermediate, and long-term levels of problems, and each will be compared with baseline (T1).

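### The field test 2 item-responsiveness criterion requires improvement to a visit that is not scheduled, which is the wrong direction for treatment side-effect items

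*Protocol article*

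**What the plan says.** Row 1 of Table 1 (Item analysis) has this purpose: "Identify items for possible elimination due to weak psychometric performance". Its item-level criteria cover every item. The third is "evidence of item responsiveness as assessed by significant improvement between baseline and test of cure assessments (field test 2 only").

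The field test 2 section on analyses and statistical considerations then fixes the reference point: "The pretumor resection assessment (T1) will be at diagnosis and is considered our baseline assessment". It adds: "Patients are not expected to have any treatment-related problems at this point". The three later time points are "intended to capture short-term, intermediate, and long-term levels of problems, and each will be compared with baseline (T1").

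Table 2 lists four assessments: before resection (T1), 4 to 10 days after it (T2), within 1 month after induction therapy ends, or 8 weeks after resection for low-risk patients (T3), and within 1 month before the 1-year cystoscopy or at early cessation (T4). None is called a test of cure, and the term appears nowhere else in the article.

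On the role of field test 2, the article says: "The final field test will be undertaken to evaluate the item-reduced version of the NMIBC-SI for reliability, validity, and responsiveness".

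**The concern.** The criterion and the design point in opposite directions for part of the instrument. According to the Results section, the index covers side effects of contemporary treatments as well as symptoms. Under PRO Assessment Time Points, the index is expected to pick up symptom changes caused by particular treatments. If patients start without treatment-related problems, a side-effect item shows that it works by getting worse after T1. The criterion counts only improvement.

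The abstract makes responsiveness to differences between contemporary treatments a main property of the index. A criterion that marks responsive side-effect items as weak, and favours items for symptoms that resolve, works against that aim. The analyst would have to flag sound items or depart from a published criterion once the data are in. Because the end visit is undefined, the analyst would also have to choose it at that stage.

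**Working it through.** The plan gives no figure here, so there is none to reproduce. The check is one of logic, followed by its size under stated assumptions.

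**Logic**

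1. Baseline is T1, where treatment-related problems are not expected.
2. An item at the floor at T1 cannot improve, so its chance of meeting the criterion is 0.
3. Reading the test of cure as T4 does not help. A side-effect item can at best return to its T1 level by then. The Introduction also says that high-risk patients have maintenance for 1 to 3 years, so some may still be on treatment at 1 year.

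**Size**

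Inputs: n = 225 (field test 2 sample size), and n = 75 as an assumed equal third (225/3; the article does not fix group sizes). A two-sided 5% paired test is assumed, since Table 1 gives no level. Let d be the true worsening in units of the SD of change.

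P(significant improvement) = Φ(−1.96 − d√n)

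P(significant worsening) = 1 − Φ(1.96 − d√n)

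- d = 0.2, n = 225: d√n = 0.2 × 15 = 3.0. Improvement: Φ(−4.96) = 3.5 × 10⁻⁷. Worsening: 1 − Φ(−1.04) = 0.85.
- d = 0.2, n = 75: d√n = 0.2 × 8.66 = 1.73. Improvement: Φ(−3.69) = 1.1 × 10⁻⁴. Worsening: 1 − Φ(0.23) = 0.41.
- d = 0.5: improvement is about 0 at both sizes. Worsening is about 1.00 at n = 225 and 0.99 at n = 75.
- d = 0: improvement is Φ(−1.96) = 0.025 at either size.

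An item that does not respond at all thus meets the criterion more often than a side-effect item that responds. The worsening probabilities show what a criterion with the right direction would detect.

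**Simulation**

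Assumptions: a 1-to-4 item; affected patients scoring 2, 3 or 4 with probabilities 0.5, 0.3 and 0.2; independent scores at the two visits; n = 225; paired t-test; 1,000 runs.

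| Share affected, T1 → follow-up | Meets criterion | Significant worsening |
|---|---|---|
| 2% → 30% | 0.000 | 1.000 |
| 5% → 30% | 0.000 | 1.000 |
| 10% → 30% | 0.000 | 0.999 |
| 10% → 10% | 0.029 | 0.020 |
| 40% → 20% | 0.987 | 0.000 |

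The last row is a symptom present at T1 that resolves in half of those affected. It passes almost always.

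**The case against.** The strongest reply is that little follows from failing the criterion. Row 1 speaks of possible elimination, and responsiveness is one criterion among several. Item reduction belongs to field test 1, and field test 2 evaluates an already reduced version. The expectation at T1 is only an expectation, and the index also covers symptoms that patients may bring to T1, for which improvement is a sensible direction. All of this stands. It limits the consequence to a flag and the scope to side-effect items, but it does not make the direction right for those items.

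A second reply is that a journal article condenses a fuller document. That does not help here. The field test 1 analysis section says that Table 1 gives the tests and criteria in full, and the field test 2 section applies Table 1. The criterion is stated, and it conflicts with the stated design.

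Three stronger readings are tempting, and the article supports none of them:

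- **Valid items will be deleted, and responsiveness then reported on the same patients.** No section says so. What the article says of field test 2 points towards validating a fixed version.
- **The row 5 effect size is inflated.** Dividing the "mean change score divided by standard deviation of pretreatment scores" is a recognised statistic, and row 5 sets no direction. The T1 SD could be small if scores sit near the floor. In the simulation the ratio is about 1.9, 1.0 and 0.6 for T1 shares of 2%, 5% and 10%, each rising to 30%. But these are assumed distributions for a single item, row 5 concerns a scale, and Table 1 already limits floor effects.
- **Resection-only patients should show no material change from T1 to T3.** The article states no such hypothesis, and symptoms present at T1 might resolve.

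**Conclusion.** The concern holds for row 1, criterion 3 of Table 1. The criterion names an assessment that the schedule does not contain, and it requires the wrong direction of change for treatment side-effect items. Such an item, responding as intended, has practically no chance of meeting it (3.5 × 10⁻⁷ at 0.2 SD and n = 225; 0 if it starts at the floor). An item with no change meets it about 2.5% of the time.

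The direction follows from the article's own statements about T1 and the later visits. *Worsening* is an inference from them, not the article's word. The probabilities rest on the assumed two-sided 5% level, complete pairs and a normal approximation, and the simulated shares are illustrative. How many items are affected cannot be said without the item list.

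This should be fixed, but it does not undermine the study: the scale-level responsiveness analysis in row 5 remains workable.

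**What to change.** Replace criterion 3 with significant change in a direction pre-specified for each item, between named scheduled visits (T1 to T2, T3 or T4). The direction would be worsening for side-effect items and improvement for disease symptoms expected to resolve. Delete the test-of-cure term. State that in field test 2, which evaluates the final version, the criterion describes item performance and does not drive elimination.

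Optionally, report a standardised response mean (mean change over SD of change) beside the row 5 effect size as a sensitivity measure, in case T1 scores sit near the floor.

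The cost is rewording in Table 1, a list of expected directions by item, and a few lines of analysis code. No new visit, patient or questionnaire is needed.
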